### Sample size and power

Statistical considerations regarding sample size and study power are based on the primary endpoint CNS composite endpoint event (CNS-CE). In Mayo Clinic’s experience, the time to CNS-CE for the Sx-SRS group is about six months. Using the log-rank test with a one-sided alpha level of 0.10 a total of 116 evaluable patients (58 in Group A and 58 in Group B) will provide 90% power to detect at least a four-month increase in median time to CNS-CE event from 6.0 months to 10.0 month in Arm B (post-operative SRS) versus Arm A (pre-operative SRS) (EAST 6.4). The final analysis will be conducted when 104 events have occurred; or when all patients are either censored or have been followed for at least 24 months, whichever occurs first. We anticipate accruing an additional 24 patients to account for ineligibility, non-evaluability, and cancellations. This design has a 46.2% chance of stopping early if there is no difference between the treatment groups and only a 2.5% chance if the Sx-SRS group has a greater time to CNS-CE event time than the SRS-Sx group. Note: In this patient population, the expected drop-out rate due to lost-to-follow-up is less than 2%; therefore, most patients are expected to be evaluable for the primary and secondary endpoints.

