### Data management and statistical analysis

All data will be entered into electronic case report forms (eCRF’s) through the Medidata Rave system. Case report forms will be automatically rolled out based on a predetermined and visit-based schedule to improve study staff workflow and data quality. Data will be exported nightly to a secure FTP for analysis and reporting.

The main objective is to assess whether patients with brain metastases who meet the eligibility criteria experience a longer time until a combined outcome of negative events, such as local recurrence, leptomeningeal disease, or symptomatic radiation brain necrosis, when they undergo SRS before surgery compared to those who undergo surgery before SRS.

Efficacy analysis will be based on the intention-to-treat principle with all eligible patients belonging to the treatment group to which they were randomized. A sensitivity analysis will also be performed based on the treatments received, comparing pre-operative SRS to post-operative SRS. Based on cavity size, a sensitivity analysis will also be performed for patients assigned to post-operative SRS who cannot receive post-operative SRS.

Interim Analysis: One interim futility analysis will be conducted when 50% (52 events) of the CNS-CE events have occurred (approximately 35 months after the study opens). If the hazard ratio comparing Arm A (pre-operative SRS) to Arm B (post-operative SRS is greater than 1.032, we will conclude that the SRS-Sx (pre-operative) treatment is not superior to Sx-SRS (post-operative) and report that the result; otherwise, conclusions will wait until the end of the study.

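### The 2.5% chance of stopping at the futility look is attached to the wrong arm: it applies when pre-operative SRS is better, not when post-operative SRS is better

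*Protocol article*

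**What the plan says.** Under *Sample size and power*, the protocol puts the control experience as follows: "the time to CNS-CE for the Sx-SRS group is about six months". The test is specified by "Using the log-rank test with a one-sided alpha level of 0.10", and the design "will provide 90% power to detect at least a four-month increase in median time to CNS-CE event", described as a change "from 6.0 months to 10.0 month in Arm B (post-operative SRS) versus Arm A (pre-operative SRS". On timing, "The final analysis will be conducted when 104 events have occurred". The same paragraph then gives two probabilities of stopping early: 46.2% if the groups do not differ, and "only a 2.5% chance if the Sx-SRS group has a greater time to CNS-CE event time than the SRS-Sx group".

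The rule behind those probabilities stands under *Data management and statistical analysis*, in the interim analysis paragraph. One futility look takes place at 52 events. If the hazard ratio of Arm A to Arm B "is greater than 1.032, we will conclude that the SRS-Sx (pre-operative) treatment is not superior to Sx-SRS (post-operative". That paragraph also fixes the labels: SRS-Sx is the pre-operative arm and Sx-SRS is the post-operative arm.

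**The concern.** A futility rule should fire rarely when the experimental sequence works and often when it is worse than control. The printed sentence says the opposite. It gives a smaller stopping probability when the control sequence, Sx-SRS, is truly better than when the arms are equal. The two figures cannot both belong to the rule as the protocol states it.

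These probabilities are the only description in the article of how its one interim decision rule behaves. Read literally, they say that the trial would almost never stop if pre-operative SRS were worse. They also leave out what a reader most needs to know about a futility look, namely the risk of abandoning pre-operative SRS when it has the effect for which the trial is powered.

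**Working it through.** **Inputs.** From *Sample size and power*: medians of 6.0 and 10.0 months, one-sided alpha 0.10, power 90%, 116 evaluable patients (58 per arm), 104 final events, and stated stopping probabilities of 46.2% and 2.5%. From the interim analysis paragraph: 52 events, stop if HR (A/B) > 1.032.

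**Direction, without arithmetic.** The chance that the estimated A/B hazard ratio exceeds 1.032 rises with the true A/B hazard ratio. A longer time in Sx-SRS (Arm B) means a true ratio above 1. The stopping probability in that scenario must therefore be higher than under no difference. On the protocol's own figure that means above 46.2%, so it cannot be 2.5%.

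**Design check.** With exponential times, the design alternative is HR (A/B) = 6/10 = 0.6.
- The Schoenfeld formula gives 4 × (1.2816 + 1.2816)² / (ln 0.6)² = 101 events and the Freedman formula gives 106, against 104 stated.
- Power at 104 events is 90.7%, or 89.9% allowing for the futility look, against 90% stated.

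The design is therefore reproduced with pre-operative SRS as the better arm.

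**Stopping probability.** With 1:1 allocation, the variance of the log hazard ratio at 52 events is about 4/52, so

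P(stop) = 1 − Φ[(ln 1.032 − ln HR) × √(52/4)], with ln 1.032 = 0.0315 and √13 = 3.606.

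| True HR (A/B) | Meaning | z | P(stop) | Protocol's figure |
|---|---|---|---|---|
| 0.6 | pre-operative better, 10 vs 6 months | (0.0315 + 0.5108) × 3.606 = 1.955 | 2.5% | 2.5%, but given for the opposite arm |
| 1.0 | no difference | 0.0315 × 3.606 = 0.114 | 45.5% | 46.2% |
| 1.1 | post-operative better | (0.0315 − 0.0953) × 3.606 = −0.230 | 59.1% | – |
| 1.25 | post-operative better | (0.0315 − 0.2231) × 3.606 = −0.691 | 75.5% | – |
| 1.5 | post-operative better | (0.0315 − 0.4055) × 3.606 = −1.348 | 91.1% | – |
| 1.667 | design effect mirrored | (0.0315 − 0.5108) × 3.606 = −1.728 | 95.8% | – |

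The 2.5% is reproduced at HR 0.6. The null figure comes within 46.2 − 45.5 = 0.7 percentage points.

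**Robustness.** If only 40% of the events fall in one arm, the result is 2.8% at HR 0.6 and 95.5% at HR 1.667. A simulation of the Cox hazard ratio at 52 events (3,000 runs per scenario, exponential times) gave 3.1% at HR 0.6, 44.9% at HR 1.0 and 95.0% at HR 1.667. None of these variations brings the post-operative-better scenario anywhere near 2.5%.

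**The case against.** The strongest defence is that nothing operational depends on the sentence. The rule in the interim analysis paragraph names the arms, the event count, the boundary and the conclusion, all in the right direction. The decision will follow that rule and not the descriptive probability. This stands: no analysis, boundary or sample size is affected. It limits the consequence but does not make the sentence true.

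Three stronger readings are tempting, and the documents do not support them.

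- A reader might infer that the correct figure for the printed scenario is about 96%, an error of more than 90 percentage points. The protocol gives no effect size for a post-operative advantage. The 96% needs the design effect mirrored to HR 1.667; at HR 1.1 the figure is about 59%.
- A reader might count the 6.0-to-10.0-month sentence as a second reversal. Read in order it assigns 6.0 months to Arm B and 10.0 to Arm A, which agrees with the six-month control median in the same paragraph. It is awkward but not wrong.
- A reader might infer that the data and safety monitoring board has been misinformed. The full protocol and the board's material are not shown, so whether the reversal appears there is unknown.

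One could also try to rescue the sentence by reversing the boundary instead. That fails, because crossing the boundary leads to the conclusion that pre-operative SRS is not superior, which fits only an A/B ratio above 1.032.

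**Conclusion.** The sentence is wrong as written. The 2.5% is the probability of stopping when pre-operative SRS is better at the design alternative, and the sentence names the opposite arm. For the scenario that it does name, the probability exceeds about 45% for any post-operative advantage, so the printed figure is too low by at least about 45.5 − 2.5 = 43 percentage points. How much more depends on an effect size that the protocol does not state.

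The direction of the error follows from the rule alone. The sizes rest on a normal approximation with equal allocation, and the hazard ratio of 0.6 on exponential times. The fault is a reversed label in the stated operating characteristic of the only interim rule. It is not a fault in the rule or in the sample size calculation.

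**What to change.** Exchange the two arm labels in the sentence and name the alternative to which the figure belongs. For example: *If pre-operative SRS (SRS-Sx) lengthens the median time to CNS-CE from 6 to 10 months (hazard ratio 0.6, Arm A to Arm B), the probability of stopping at the interim look is 2.5%.* If the sponsor also wants to report the case in which post-operative SRS is better, the assumed hazard ratio should stand beside the figure.

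As an optional clarity edit, the effect sentence could state the two medians arm by arm.

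The cost is one sentence. The boundary of 1.032, the 52 and 104 events and the 116 evaluable patients stay as they are. According to *Trial status*, 65 patients had been enrolled and the interim criteria had not been met at submission, so on the article's own account the look had not yet taken place. The sponsor can check at the same time whether the full protocol carries the same wording.

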## Discussion

Emerging retrospective and prospective data have demonstrated some of the theoretical benefits of preop SRS vs. postop SRS [14–18]. At the time of this publication, we are aware of two ongoing Phase 2 clinical trials [19, 20] and five additional ongoing Phase 3 randomized clinical trials actively enrolling patients NCT03741673 (MD Anderson, enrolment target = 110), NCT04474925 (Alberta, enrolment target = 88), NCT05124236 (Multicentric International Europe, enrolment target = 200), NCT05438212 (NRG Oncology NCI, enrolment target = 236), NCT05545007 (IRCCS Istituto Clinico Humanitas, Milano, Italy, enrolment target = 170). The current study NCT03750227 has an enrolment target of 140 patients and will provide information on whether there is an increase in the time to a composite endpoint of occurrence of either: local recurrence, leptomeningeal disease, or symptomatic radiation brain necrosis in patients who receive SRS prior to surgery as compared to patients who receive surgery prior to SRS. Additionally, the study will compare overall survival; patient-reported outcomes; morbidity; completion of planned therapies; time to systemic therapy; time to regional progression; time to CNS progression; time to subsequent treatment; rate of radiation necrosis; rate of local recurrence; and rate of leptomeningeal disease for pre-op vs. post-op SRS.

As designed, our study design has multiple limitations, some of which are addressed in other ongoing studies: Primary among these is the inflexibility of the radiation dose and fractionation. Dosing for MC167C builds upon the experience of NCCTG N107C/CEC·3 [9], which compared post-operative SRS to post-operative WBRT. This dosing paradigm means that some of the largest eligible lesions may be treated with as little as 12 Gy radiation, potentially creating hesitation to enroll patients with large lesions on this protocol. This challenge could be addressed via dose escalation especially in pre-operative radiation; wherein irradiated tissue, including some surrounding brain tissue, is intentionally resected when safely achievable but is not permitted on our protocol. Alternatively, fractionation may enable larger lesions to be safely treated to more biologically effective radiation doses. The ongoing FRACTIONATE study (NCT05222620) directly compares single fraction versus fractionated radiosurgery to treat surgical cavities; fractionated radiation is utilized in the post-operative arm for NCT05124236 and in both the pre-and post-operative arms for NCT05545007.

We are heartened by the strong interest in evaluating neoadjuvant SRS, as evidenced by the multiple active trials addressing this important question. We look forward to managing patients in the future based on the results of these rigorously designed randomized studies.

### Trial status

At the time of manuscript submission, the trial status is recruiting. Sixty-five patients have been enrolled. Criteria for interim analysis still need to be met.

### Safety considerations

Depending on random study selection, the Cancer Center Auditing area will review the trial bi-annually or yearly to assess accrual, adverse events, and any endpoint problems. Any safety issues requiring protocol changes will be communicated through protocol amendments.

This study will be reviewed in conjunction with the Mayo Clinic Cancer Center Data and Safety Monitoring Board (DSMB) processes as an interventional study. Any safety issues requiring protocol changes will be communicated through protocol amendments.

The principal investigator and the statistician will review the study at least twice a year to identify accrual, adverse events, and any endpoint problems that might develop.

### Follow-up

All enrolled patients will be followed up for a total of 5 years. For the first two years, post treatment patients will receive active monitoring every three months, undergoing history, physical and neurological exam, including weight, medication review and ECOG performance status, MRI, and adverse events assessment. After two years, patients will be monitored for key study events such as progression, new primaries, and death up to 5 years post enrolment.

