### Randomization

The balancing algorithm that we will use is a dynamic allocation procedure that is part of iMedidata Rave, known as Balance. After stratification (Fig. 1), patients will be randomized at a 1:1 ratio between:**Arm A:** Pre-op SRS followed by surgery (within two weeks post-SRS).**Arm B:** Surgery followed by post-op SRS (within four weeks of surgery).

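### MRI visits counted from end of treatment, with unequal treatment windows and no stated time origin, can bias the log-rank test, probably against pre-operative SRS

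*Protocol article*

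**What the plan says.** The Follow-up section of the protocol article states: "For the first two years, post treatment patients will receive active monitoring every three months". These visits include the MRI. The same paragraph counts the five-year limit from enrolment, so it uses two different anchors.

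The Randomization section gives the arms different windows. Arm A is "Pre-op SRS followed by surgery (within two weeks post-SRS"; Arm B is "Surgery followed by post-op SRS (within four weeks of surgery".

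Under Primary goals, radionecrosis is defined on MRI (only symptomatic necrosis counts in the composite), and leptomeningeal disease is a radiological diagnosis unless CSF cytology is available. Sample size and power specifies the primary comparison: "Using the log-rank test with a one-sided alpha level of 0.10". Data management and statistical analysis compares the arms as randomised and sets one futility look at 52 events, with a hazard ratio (HR) boundary of 1.032.

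Four things are not stated: the time origin of CNS-CE, the wait from randomisation to first treatment, how an event is dated, and whether the post-treatment visits count from the second of the two treatments.

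**The concern.** A scan-detected event carries the date of the scan, not the date the disease appeared. If the visit calendar starts when treatment is complete, and one arm tends to complete later, that arm's scans come later on a clock that starts at randomisation. Identical disease is then dated earlier in Arm A at each visit cycle. The log-rank test uses only the order of event times, so even a short but consistent stagger counts against Arm A.

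Two things are at stake. The trial could lose power to show a real benefit of pre-operative SRS, and the futility rule could stop an effective arm more often than planned.

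**Working it through.** **1. The plan's own figure.** Inputs from Sample size and power: one-sided alpha 0.10; medians "from 6.0 months to 10.0 month in Arm B (post-operative SRS) versus Arm A (pre-operative SRS"), which is HR 6/10 = 0.60 under exponential times; and "a total of 116 evaluable patients (58 in Group A and 58 in Group B) will provide 90% power". On the event count: "The final analysis will be conducted when 104 events have occurred".

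- Schoenfeld: 4 × (1.2816 + 1.2816)² / (ln 0.60)² = 26.28 / 0.2609, rounded up to 101 events.
- Freedman: (2.5631)² × (1.6/0.4)² = 6.570 × 16, rounded up to 106 events.
- Power with 104 events: Φ(0.5108 × √104 / 2 − 1.2816) = Φ(1.323) = 0.907.

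The stated 104 events lie between the two formulas, so the design reproduces.

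**2. Size of the stagger.** Assume first treatment starts equally soon in both arms. If completion is spread evenly over each window, mean completion is 1 week in Arm A and 2 weeks in Arm B, a mean shift of 1 week. The largest shift is 4 − 0 = 4 weeks. The windows are maxima and they overlap.

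**3. Effect on the log-rank test.** Simulation with 4,000 trials per scenario: 58 patients per arm, entry uniform over 4.5 years, exponential times from randomisation, no deaths. Events are dated at the next three-monthly scan counted from end of treatment, with visit jitter of ±0.25 month. Follow-up stops at 104 events or 27 months per patient. With half of events scan-dated, the rest carry their true dates.

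| End of treatment (weeks) | Scan-dated | Null HR | Type I error | Power | Estimated HR at true 0.60 |
|---|---|---|---|---|---|
| A 4, B 4 (same clock) | all | 1.00 | 0.10 | 0.90 | 0.59 |
| A 2, B 4 | all | 1.16 | 0.024 | 0.77 | 0.66 |
| A 2, B 4 | half | 1.05 | 0.062 | 0.88 | 0.61 |
| A 0.2, B 4 | all | 1.11 | 0.043 | 0.80 | 0.64 |
| A 0.2, B 4 | half | 1.03 | 0.079 | 0.87 | 0.61 |
| A uniform 0–2, B uniform 0–4 | all | 1.07 | 0.055 | 0.85 | 0.62 |
| A uniform 0–2, B uniform 0–4 | half | 1.03 | 0.086 | 0.89 | 0.60 |
| A 2, B 1 (reversed) | all | 0.90 | 0.24 | 0.96 | 0.53 |

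A second simulation gave a null HR of 1.06–1.16 and power of 0.80–0.88 with all events scan-dated, and 1.03–1.06 and 0.88–0.90 with about 60% scan-dated.

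Three readings follow. Three-monthly scanning on a common clock does no harm. The bias does not grow steadily with the gap: a fixed two-week gap does more than a gap of nearly four weeks, because order within a visit cycle matters more than distance. With every scan exactly on its due date, the two-versus-four-week case reaches null HR 1.21 and power about 0.74. Real visits are not that regular, so this is left out of the range.

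**4. Futility look.** The standard error of ln HR at 52 events is 2/√52 = 0.277. The chance of exceeding 1.032 is 1 − Φ((ln 1.032 − ln HR)/0.277):

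- HR 1.00: 1 − Φ(0.114) = 45% (article: 46.2%).
- HR 0.60: 1 − Φ(1.955) = 2.5%.
- Estimate pulled to 0.66: 1 − Φ(1.612) = 5.3%.
- Estimate pulled to 0.67: 1 − Φ(1.558) = 6.0%.

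**The case against.** A reader might infer that every Arm B scan falls two to four weeks after its Arm A counterpart, so that bias against pre-operative SRS is established. The article does not support that:

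- The origin of CNS-CE is not given. If time runs from end of treatment, the stagger disappears.
- The post-treatment wording may only describe patients who are in follow-up. The full protocol, not shown here, may settle both the origin and the calendar.
- Two weeks is the difference between the two maxima, not a minimum shift. The wait to first treatment is unknown, so the gap could be zero or reversed.
- Symptomatic necrosis, symptomatic recurrence and CSF-positive leptomeningeal disease can be found between scans, which dilutes the effect.

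All of this stands, and it makes the point conditional. It does not remove it. The article itself suggests the direction: the correlative aim studies tissue irradiated 24 to 48 hours before resection, and the expected outcomes cite a condensed timeline for pre-operative SRS. An end-of-treatment origin is no clean escape either. It lies after randomisation and depends on the arm, and the analysis section foresees Arm B patients who cannot receive SRS and so have no such date.

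Two other inferences should be resisted. Under no true difference, a null HR of 1.07–1.13 raises the chance of a futility stop from 45% to 55–63%, but stopping is then the correct decision; the figure that matters is the one at HR 0.60. Nor does the bias argue for an interval-censored primary test. An interval-censored Weibull model rejected 14% of null trials at a nominal 10% in 500 runs. The simulation standard error is √(0.1 × 0.9/500) = 1.3 points, so the excess is about three standard errors.

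**Conclusion.** The concern holds conditionally. As worded, the article lets assessment dates depend on the arm and does not fix the time origin that would show whether this matters. If CNS-CE runs from randomisation and first treatment starts equally soon in both arms, the log-rank test is probably biased against pre-operative SRS. The null HR is about 1.03–1.16, power is about 0.77–0.90 against the stated 0.90, and the risk of a wrong futility stop at HR 0.60 is at most about 5–6% against 2.5%.

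The unfavourable end needs nearly all events to be scan-dated and a consistent gap between the arms. The favourable end is close to the design. In the expected direction the bias is conservative and would not create a false claim of superiority. If Arm A finished later it would: a one-week reversal gives a type I error of 0.24 in place of 0.10. These sizes rest on exponential times, no deaths and the assumed visit jitter.

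**What to change.** State that CNS-CE is timed from randomisation in both arms. For patients still to be enrolled, count the research MRI visits from randomisation in both arms. Treatment windows and clinically indicated imaging are unaffected. Keep the log-rank as the primary test and pre-specify an interval-censored sensitivity analysis, from last negative to first positive MRI, which also covers patients already enrolled.

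The cost is revised visit-window wording, one extra analysis, and a mixed calendar because the 65 patients enrolled at submission (of 140 planned) follow the existing one. The article reports that the criteria for the interim analysis had not been met at submission, so it is best settled before that look.

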### Data management and statistical analysis

All data will be entered into electronic case report forms (eCRF’s) through the Medidata Rave system. Case report forms will be automatically rolled out based on a predetermined and visit-based schedule to improve study staff workflow and data quality. Data will be exported nightly to a secure FTP for analysis and reporting.

The main objective is to assess whether patients with brain metastases who meet the eligibility criteria experience a longer time until a combined outcome of negative events, such as local recurrence, leptomeningeal disease, or symptomatic radiation brain necrosis, when they undergo SRS before surgery compared to those who undergo surgery before SRS.

Efficacy analysis will be based on the intention-to-treat principle with all eligible patients belonging to the treatment group to which they were randomized. A sensitivity analysis will also be performed based on the treatments received, comparing pre-operative SRS to post-operative SRS. Based on cavity size, a sensitivity analysis will also be performed for patients assigned to post-operative SRS who cannot receive post-operative SRS.

Interim Analysis: One interim futility analysis will be conducted when 50% (52 events) of the CNS-CE events have occurred (approximately 35 months after the study opens). If the hazard ratio comparing Arm A (pre-operative SRS) to Arm B (post-operative SRS is greater than 1.032, we will conclude that the SRS-Sx (pre-operative) treatment is not superior to Sx-SRS (post-operative) and report that the result; otherwise, conclusions will wait until the end of the study.

